#### Data collection for the content validation

Content validation will be performed to assess the clinical relevance and the representativeness of the practice of interprofessional teams in post-operative cardiac surgery setting of the items of the extraction tool. Content validation will follow two steps [46]. First, an expert committee will be recruited from clinicians, managers, and researchers who have expertise in postoperative cardiac surgery. The identification and recruitment of experts will be conducted by our research team and will include experts in Canada. A total of 10 experts will be recruited, including at least the following five: 1) an ACNP who worked a minimum of one year within a postoperative cardiac surgery unit outside of our associated UHC, 2) a cardiac surgeon or fellow in cardiac surgery who worked at least two years in an acute care centre outside of our associated UHC, 3) a nurse manager who has led for at least one year, a postoperative cardiac surgery unit, within our associated UHC, 4) a healthcare professional who worked in the data warehouse of our associated UHC for at least one year, and 5) a researcher in nursing or healthcare sciences with an expertise in measurement instruments and/or cardiac surgery.

Second, an electronic survey [47] will be created and sent to each expert of the committee. The survey will be composed of all items of the extraction tool (best-practice guidelines and confounding variables). For each item, experts will assess its relevance using a 5-points Likert scale [48, 49]. Additional spaces for qualitative comments and suggestions will be included in the survey. Two rounds of revision are planned. After the first round, our team will update the extraction tool and revise any unclear items based on the experts’ recommendations, and an updated version will be resubmitted to the expert committee.

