### Data analysis

Statistical analysis will be conducted to meet objectives one, two and three. The unit of observation will be the patient-level and the unit of analysis will be the interprofessional team with or without ACNP-level.

#### Objective 1

For the content validation [56, 57], a Fleiss Kappa will be calculated for each round of revision and a value between 0.60 and 0.80 will be targeted [48, 49]. The content validity index (CVI) of each individual item of the extraction tool will be calculated from the proportion of experts who rated a score of 4 or 5 on the Likert scale [58]. A CVI of 0.80 will be targeted for each item and items with a value below 0.80 will be removed or modified. Then, the proportion of items with a CVI value above 0.80 will be calculated to determine the overall CVI of the extraction tool. A value higher than 0.80 for the overall CVI of the extraction tool will be targeted [46]. Qualitative comments and recommendations by experts will be analyzed by content analysis [59].

For the criterion validation, Spearman correlation will be calculated to assess the correlation between the measures of the gold standard (e.g., the performance measures of the STS), and the measures of the extraction tool. Values of Spearman correlation higher than 0.70 will be targeted [48, 49].

#### Objective 2

Descriptive analysis will be performed to assess the level of adherence by interprofessional teams with and without ACNPs, as well as the confounding variables for patients under the care of both teams [60]. A graphic illustration will be created to visualize the tendency and distribution of the level of adherence to best-practice guidelines by interprofessional teams with and without ACNPs. An analysis of missing data will be conducted to examine the quality and distribution of missing data within patient health records and electronic databases. Team meetings and consultations with clinicians and statisticians will be held to discuss and identify potential causes of missing data, as well as to conduct a statistical analysis to manage them [61]. Bivariate analysis will be conducted, and the statistical significance will be based on a *p*-value of 0.05 [60]. The Bonferroni correction will be applied for the examination of each confounding variable related to the patient and interprofessional teams’ characteristics [62].

#### Objective 3

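### The Fleiss kappa target of 0.60–0.80 is out of reach on the CVI's own relevant/not-relevant split once every item passes, and the two CVI rules disagree about an item at exactly 0.80

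*Protocol article*

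**What the plan says.** All of this is in the protocol article, under Data collection for the content validation and under Data analysis, Objective 1.

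- **Panel and scale.** "A total of 10 experts will be recruited". On the ratings: "For each item, experts will assess its relevance using a 5-points Likert scale". Two rounds are planned, and the tool is updated between them.
- **Agreement target.** "a Fleiss Kappa will be calculated for each round of revision and a value between 0.60 and 0.80 will be targeted". The article does not say whether kappa uses all five categories or a split.
- **Item CVI.** It is defined as "the proportion of experts who rated a score of 4 or 5 on the Likert scale", so ratings are split into 4–5 and 1–3. The rule is "A CVI of 0.80 will be targeted for each item and items with a value below 0.80 will be removed or modified".
- **Overall CVI.** "the proportion of items with a CVI value above 0.80 will be calculated to determine the overall CVI", with this target: "A value higher than 0.80 for the overall CVI of the extraction tool will be targeted".

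**The concern.** Fleiss kappa compares observed agreement with the agreement expected from the pooled share of each category. If nearly all ratings fall in one category, expected agreement is already close to 1, and kappa is small however well the experts agree. The item-CVI rule pushes the tool towards that state, because it removes or repairs any item that fewer than eight of ten experts rate 4 or 5. On that split the two targets pull in opposite directions.

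The two CVI rules also meet badly at 0.80. With ten experts the CVI moves in steps of 0.10, so 0.80 is an attainable and fairly common value. The item rule acts below 0.80, while the overall count credits only items above it.

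At stake is how objective 1 is reported. The tool supplies the composite score that is the dependent variable of the objective 3 regression. A tool that the experts endorse could be reported as having poor agreement, or as missing its overall CVI target.

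**Working it through.** **Inputs.** From the article: 10 experts; a five-point scale; CVI split at 4–5; item threshold 0.80; overall target above 0.80; kappa target 0.60–0.80. Assumed: 25 items, one for each of the 12 guidelines and 13 confounding variables (12 to 100 items also tried). The thresholds are targets and not derived figures, so there is no result of the plan's own to reproduce.

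**Formula.** For item i with counts n_ij over categories j and m = 10 raters:
- P_i = (Σ n_ij² − m) / (m(m − 1))
- P_e = Σ p_j², where p_j is the pooled share of category j
- kappa = (mean P_i − P_e) / (1 − P_e)

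**1. Relevant/not-relevant split, every item at 8/10, 9/10 or 10/10.** All combinations were enumerated. For 25 items the maximum comes from 24 items at 10/10 and one at 8/10:
- P_i at 8/10 = (64 + 4 − 10)/90 = 0.6444; mean P_i = (24 + 0.6444)/25 = 0.98578
- pooled relevant share = 248/250 = 0.992; P_e = 0.992² + 0.008² = 0.98413
- kappa = (0.98578 − 0.98413)/(1 − 0.98413) = **0.104**

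The maximum is 0.096 for 12 items, 0.107 for 40 and 0.109 for 100. A general bound follows. If no item has more than 20% not-relevant ratings, kappa ≤ 1 − 0.8·m/(m − 1) = 1 − 0.8 × 10/9 = 0.111. With 24 items at 10/10 and one at 9/10, kappa is −0.004. With all 25 at 10/10, P_e = 1 and kappa is 0/0.

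**2. Same split, failing items still present (possible in round one).** Take 12 items at 10/10, nine at 9/10 and four at 1/10:
- mean P_i = (12 + 13 × 0.8)/25 = 0.896
- relevant share = (120 + 81 + 4)/250 = 0.82; P_e = 0.82² + 0.18² = 0.7048
- kappa = 0.1912/0.2952 = 0.65, and overall CVI = 21/25 = 0.84

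Both targets are met, but only because four items fail the item rule.

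**3. Five categories, every item at CVI 1.00.** Let 13 items be mostly 5 and 12 mostly 4, with the dissenting experts giving the other of these two scores.

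| Experts giving the identical score | Fleiss kappa |
|---|---|
| 10 of 10 | 1.00 |
| 9 of 10 | 0.60 |
| 8 of 10 | 0.29 |
| 7 of 10 | 0.07 |

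At nine of ten, P_e = (129/250)² + (121/250)² = 0.5005, and kappa = (0.8 − 0.5005)/0.4995 = 0.60. If 23 items are mostly 5 and two mostly 4, nine-of-ten agreement gives only 0.27.

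Simulation with 25 items, all passing the item rule, agrees. Item profiles were drawn from a Dirichlet distribution averaging 90% rated 4–5, and only items with CVI of at least 0.80 were kept. Mean kappa was about 0 when items did not differ. It was about 0.22 when an average of 7 to 7.5 experts shared the most common score on an item. It reached about 0.65 only when that average was about nine.

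**4. The 0.80 boundary.** Let X be the number of ten experts rating an item 4 or 5, binomial with true rate p and independent ratings. Given that an item passes (X ≥ 8), the chance that it also counts as above 0.80 is r = P(X ≥ 9)/P(X ≥ 8). The overall CVI exceeds 0.80 only if at least 21 of 25 items count, since 20/25 is exactly 0.80.

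| p | P(X = 8) | r | P(at least 21 of 25 count, given all pass) |
|---|---|---|---|
| 0.95 | 0.075 | 0.924 | 96% |
| 0.90 | 0.194 | 0.792 | 38% |
| 0.85 | 0.276 | 0.664 | 4% |

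**The case against.** The 0.10 ceiling needs two conditions that the article does not state together: kappa computed on the 4–5 split, and every item already passing. The split is applied in the text to the CVI alone, and the data collected are five-point ratings, on which 0.60 or more is attainable with every item at CVI 1.00. Kappa is calculated on whatever items are rated in each round. Low-CVI items are still present in round one, and a modified item can fail again in round two. Assuming identical rating probabilities for all items drives kappa to zero by construction, so that case alone proves nothing about items that differ.

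All of this stands, and it rules out two stronger readings. A reader might infer that the kappa and CVI targets can never be met together; steps 2 and 3 show that they can. A reader might also infer that the tool would fail content validation, or that a low kappa would force items to be revised. The text says only that the value is targeted. Removal or modification follows from the item CVI, and the update between rounds follows the experts' recommendations.

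Two things survive. Step 2 meets the kappa target only with items that the item rule would remove or modify, and step 3 needs near-unanimity on whether an item is a 4 or a 5, a distinction that the CVI ignores. The objection does not touch the 0.80 mismatch.

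The point is also limited in reach: it changes neither the cohort, the matching nor the regression.

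**Conclusion.** The point holds in a limited form. On the split that defines the CVI, with ten experts and every item at 0.80 or higher, Fleiss kappa cannot exceed about 0.10–0.11, against a target of 0.60–0.80, and it is undefined under full endorsement. That ceiling hardly depends on the assumed 25 items. On five categories the target is attainable, but it needs about nine of ten experts to give the identical score and items to divide fairly evenly between mostly-4 and mostly-5. Full consensus there gives 1.00, above the stated upper end. An endorsed tool would therefore probably miss the agreement target in round two. That is a judgement about likely rating patterns, and the article gives the miss no consequence.

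The CVI mismatch follows from the wording alone. Its size rests on 25 items, independent ratings and a common true relevance rate: a tool whose every item passes exceeds the overall target with a chance of 96%, 38% or 4% at rates of 0.95, 0.90 or 0.85.

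**What to change.** - **CVI rules.** Use 0.80 or higher both for keeping an item and for counting it towards the overall CVI. A tool whose every item passes then has an overall CVI of 1.00.
- **Agreement.** Replace the Fleiss kappa target with a measure not driven by prevalence. One choice is the modified kappa for each item, k* = (CVI − Pc)/(1 − Pc), with Pc = C(10, A) × 0.5¹⁰ and A the number of experts rating 4 or 5. At 8/10, Pc = 45/1024 = 0.044 and k* = (0.80 − 0.044)/0.956 = 0.79. Gwet's AC1 across items is another.
- **If Fleiss kappa is kept,** state the scale on which it is computed and report it descriptively, without the 0.60–0.80 target.

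The cost is about two sentences, with the same survey data. The one downside is a less direct comparison with studies that report Fleiss kappa.

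### The item rule and the overall CVI use different cut-offs at exactly 0.80, a value that 10 experts can produce, and the item set and round for the overall CVI are not fixed

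*Protocol article*

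**What the plan says.** All references are to the protocol article.

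- **Panel and scale** (Data collection for the content validation): "A total of 10 experts will be recruited". "For each item, experts will assess its relevance using a 5-points Likert scale". Two rounds are planned. After the first, the team updates the tool and sends it back to the experts.
- **Item CVI** (Data analysis, Objective 1): "calculated from the proportion of experts who rated a score of 4 or 5 on the Likert scale".
- **Item rule** (same section): "A CVI of 0.80 will be targeted for each item and items with a value below 0.80 will be removed or modified".
- **Overall CVI** (next sentence): "Then, the proportion of items with a CVI value above 0.80 will be calculated to determine the overall CVI of the extraction tool".
- **Overall target** (next sentence): "A value higher than 0.80 for the overall CVI of the extraction tool will be targeted".

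The section says that the Fleiss kappa is calculated for each round. It does not say for which round the overall CVI is calculated, or whether its denominator is all items rated or only those kept.

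**The concern.** The item rule and the tool rule sit next to each other and treat the value 0.80 differently. An item at exactly 0.80 meets its own target and needs no action, yet it does not count among the items above 0.80 that make up the overall CVI. A tool in which every item satisfied the plan could therefore miss the tool-level target.

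The order of the sentences adds a second difficulty. The overall CVI is introduced by *Then*, directly after the step in which low items are removed or modified, so it can be read as calculated on the items that survive. That would select items on the same quantity that is afterwards summarised.

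At stake is the tool-level content-validity figure. Developing the tool is the first objective, and the Discussion promises the tool to the wider research community. If the cut-off and item set are settled only after the ratings are in, whether the target is met can depend on that choice.

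**Working it through.** The plan gives thresholds but no computed CVI, so there is no figure to reproduce.

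**1. Attainable values.** With 10 raters the item CVI is k/10, so it takes the values 0.0, 0.1, …, 1.0. The value 8/10 = 0.80 can occur. The item rule passes it (not below 0.80), and the overall CVI does not count it (not above 0.80).

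**2. Fixed examples with 25 items.** The count 25 is 12 guidelines + 13 confounders (Variables under study). One item per variable is an assumption.

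| Items below 0.80 | Items at exactly 0.80 | Overall CVI, *above* | Overall CVI, *at or above* |
|---|---|---|---|
| 0 | 4 | 21/25 = 0.84 (meets > 0.80) | 25/25 = 1.00 |
| 0 | 5 | 20/25 = 0.80 (misses) | 25/25 = 1.00 |
| 0 | 25 | 0/25 = 0.00 (misses) | 25/25 = 1.00 |
| 3 | 0 | 22/25 = 0.88 (meets) | 22/25 = 0.88 |
| 3 | 3 | 19/25 = 0.76 (misses) | 22/25 = 0.88 |

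In the first three rows every item satisfies the item rule. The last two rows show items that were modified, rated again and stayed low.

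**3. How often the boundary matters.** Assume that each expert independently endorses each item with the same probability p. With X ~ Binomial(10, p):

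- P(item above 0.80) = P(X ≥ 9)
- P(item at or above 0.80) = P(X ≥ 8)

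The target is a share above 0.80. For 25 items this means at least 21 (20/25 = 0.80 is not enough). The chance of meeting it on all rated items is P(Y ≥ 21), where Y ~ Binomial(25, q) and q is one of the two item probabilities.

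| p | P(X ≥ 9) | P(X ≥ 8) | Chance of meeting target, *above* | Chance, *at or above* |
|---|---|---|---|---|
| 0.85 | 0.544 | 0.820 | 0.2% | 52% |
| 0.90 | 0.736 | 0.930 | 17% | 97% |
| 0.95 | 0.914 | 0.988 | 94% | about 100% |

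At p = 0.90, P(X = 8) = 0.930 − 0.736 = 0.194. The chance that at least one of 25 items lands on exactly 0.80 is 1 − (1 − 0.194)^25, which is over 99%.

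**4. Survivors only.** Suppose every item below 0.80 is removed. The survivors score 0.8, 0.9 or 1.0.

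- With *above*, the expected overall CVI is P(X ≥ 9)/P(X ≥ 8), which is 0.66, 0.79 and 0.92 at p = 0.85, 0.90 and 0.95. The chance of meeting the target at p = 0.90 is about 45%.
- With *at or above*, the overall CVI is 1.00 at every p.

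Aligning the cut-off is therefore not enough by itself. The item set must be fixed as well.

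**5. Fewer responders.** The lowest attainable CVI at or above 0.80 is 6/7 = 0.857 with 7 raters, 7/8 = 0.875 with 8, and 8/9 = 0.889 with 9. Exactly 0.80 cannot occur with these numbers, so the two cut-offs coincide.

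**The case against.** The strongest reply is that this is a one-word slip in a condensed article, and that the rest depends on how *Then* is read. Several parts of that reply stand.

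- **Low items are not simply deleted.** The text allows removal or modification, and the updated tool goes back to the experts. A modified item can score low again, so the overall CVI is not bound to be 1.00. The rows with three low items in the first table show this.
- ***Then* may only order the calculations**, with item CVIs first and the tool-level figure second. All rated items is an available reading, and it gives the target a purpose.
- **The index is not empty.** A reader might infer that it cannot measure content validity. The documents do not support that. Even on survivors, read literally, it is the share of items endorsed by at least 9 of 10 experts, and its expected value rises from 0.66 to 0.92 as p goes from 0.85 to 0.95.
- **A reader might also infer that items changed after round 2 would carry no CVI.** The content-validation section describes an update after the first round and no revision following the second, so this is not established.
- **The consequence is limited.** The overall value is a target with no stated stop rule. Item CVIs, Fleiss kappa, expert comments, criterion validation and a pilot test are also planned.

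The mismatch at 0.80 is not answered by any of this. It is in the stated wording, it can occur with the stated number of experts, and it applies to either item set.

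**Conclusion.** The point holds as a minor error confined to Objective 1. The two rules disagree on an item at exactly 0.80, and the overall CVI is not tied to a round or an item set.

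In the illustration, the choice between *above* and *at or above* moves the chance of meeting the target on all rated items from 17% to 97% at p = 0.90, and from 0.2% to 52% at p = 0.85. At p = 0.95 the difference is small (94% against about 100%). These figures assume 25 items, all 10 experts responding, independent ratings and one endorsement probability for every item. They show the sensitivity to the wording and do not predict this panel's result. With 7, 8 or 9 responders the cut-offs coincide, and only the question of item set and round remains.

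The Objective 3 regression does not use the overall CVI, so the comparison of teams with and without nurse practitioners does not depend on it.

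**What to change.** Under Data analysis, Objective 1:

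1. Use one cut-off in both rules. An item meets its target at a CVI of at least 0.80, and the overall CVI is the proportion of items with a CVI of at least 0.80.
2. State that the overall CVI is calculated and reported for each round, on all items rated in that round, before any item is removed or modified.

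The planned proportion can stay as the summary measure.

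The cost is two sentences and no new data. The reported overall CVI may be less favourable than one calculated on retained items only.

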### Interpretation of the findings

Consultations with clinicians and managers practicing in postoperative cardiac surgery settings in Québec and Canada will be conducted to gain an in-depth understanding of the findings. These consultations will allow the research team to explore potential underlying factors and mechanisms which could influence the level of adherence to best-practice guidelines by interprofessional teams with and without ACNPs. Field notes will be taken during these consultations and analyzed using content analysis [45].

### Ethical considerations

Ethical approval was obtained prior to the beginning of the study. No identifying information will be collected during the content validation with the expert committee and the data collection within electronic databases and patient health records. A confidential pairing system will be created to match the patient identification with a random number [66]. The database of the project will be kept in a secure server, protected by a confidential numeric code known only by the research team. During the dissemination of the findings, data will be shared in an aggregated form and the identity of the UHC, as well as the identity of the patients and clinicians, will remain confidential.

## Discussion

ACNPs hold an important place within interprofessional teams caring for patients and families following cardiac surgery. For patients and families, ACNPs contribute to the management of pharmacotherapy, clinical and psychosocial conditions, as well as lifestyle promotion and teaching of coping strategies. For interprofessional teams, ACNPs enhance the collaboration and communication among team members and reinforce continuity of care. Until now studies examined the efficacy of ACNPs on patient and organization outcomes within postoperative cardiac surgery settings; however, less attention has been paid to underlying factors contributing to the effect of ACNPs on these outcomes.

The findings of this study will further our understanding of the contributions of ACNPs in interprofessional teams practising in postoperative cardiac surgery settings in Québec, Canada. This project will generate empirical data to support and document the practice of ACNPs within interprofessional teams in three important ways. Firstly, an extraction tool focusing on the level of adherence to best-practice guidelines by interprofessional teams in postoperative cardiac surgery will be available for the field of cardiac surgery research and the scientific community more broadly. Secondly, for patients under the care of interprofessional teams with and without ACNPs, the findings will provide a description of the patient and interprofessional team characteristics as well as the adherence to best-practice guidelines. Finally, this study will examine the effect of ACNPs on the adherence to best-practice guidelines in settings where ACNPs are incorporated within inter-professional teams, and provide empirical data for those settings looking to introduce such roles in a postoperative cardiac surgery setting.
